### Sample size

Based on our data from an earlier study in this population, the standard deviation of HbA1c amongst those with values 75 mmol/mol (≥9%) or greater (and irrespective of self-monitoring blood glucose frequency) was 18.6 mmol/mol [38, 39]. Assuming a correlation between repeated measures of 0.7, a sample size of 58 (29 per group) would provide 80% power to detect a difference in mean changes for HbA1c of 1% (10.93 mmol/mol) using a two-sided test at the 0.05 level. This would be considered a clinically important difference, of a similar magnitude to other proven technologies such as insulin pumps or CGM [40]. To account for a small amount of missing data and loss to follow-up (anticipated to be < 10%), we will recruit a sample size of 64 (32 participants per group) at baseline. Reasons for non-retention of participants (i.e., consent withdrawn, moving outside of the study DHBs, or lost to follow-up) will be recorded and shown in a CONSORT flow diagram (Fig. 1).

### Study procedures

#### Screening and enrolment

After being given an opportunity to review the participant information sheet and consider whether they want to be involved in the study, and prior to screening, adolescents and young adults aged 16–20 years and a parent/guardian of adolescents aged 13–15 years must provide written informed consent for their participation in the study. Parents/guardians will also be asked for their consent to provide information about themselves. Adolescents aged 13–15 years must also provide written assent for their participation. A point of care (POC; DCA Vantage Analyzer, Siemens Healthcare Diagnostics, Ireland) HbA1c will be measured when POC HbA1c has not been assessed in the previous 14 days. All female patients will provide a urine sample and study staff will follow the manufacturer’s guidelines for conducting the pregnancy test (EasyCheck® Pregnancy Test, Hangzhou Clongene Biotech Co, Ltd., China). Date of diabetes diagnosis (for subsequent calculation of duration of diabetes), current insulin regimen, insulin dosing, HbA1c measurements in previous 6 months, and co-morbidities will be recorded from electronic medical records. Diabetic ketoacidosis in the past 6 months, and severe hypoglycaemia events (defined as requiring the assistance of another person to treat [41]) in the past 6 months will also be recorded from electronic medical records to provide baseline estimates of frequency for these events. Any patient can withdraw (or be withdrawn by their parent or guardian for those aged 13–15) from the study at any point and return to their usual medical care.

#### Randomisation

Patients who give consent for participation and fulfil the eligibility criteria will be enrolled in the study and randomly allocated by an offsite biostatistician ([name]) in batches using a 1:1 ratio to either the waitlist control (SMBG) group or the intervention (FGM) group. The statistician will be blinded to allocation arm and will use non-informative group codes until all planned analyses are completed. As gender and pre-study HbA1c may significantly affect the primary outcomes, minimisation will be used (based on gender [male, female; HbA1c [75 to < 100 mmol/mol, ≥ 100 mmol/mol; 9.0 to < 11.3%, ≥ 11.3%]) and with a small random component (20%) along with randomly ordering the participants in each batch used to preserve allocation concealment. The study group will be revealed to the participant at the baseline visit after all assessments have been completed.

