#### Flash glucose monitoring acceptability

Adolescents in the FGM group will evaluate the FreeStyle Libre FGM system acceptability at 3- and 6-months, and all participants will answer acceptability questions at 12-months using a non-validated instrument adapted from previous similar research [25]. On an ordinal scale from 0 (strongly disagree) to 5 (strongly agree), participants will rate their opinion in regards to the following areas: acceptability of sensor application, wear/use of the device and comparison to SMBG.

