### Statistical analysis

Means and standard deviations (SDs) will be reported for continuous variables (i.e., age, diabetes duration, HbA1c, glucose monitoring behaviour, questionnaire scores) that are approximately normally distributed, geometric means and SDs for those that are approximately log-normally distributed, and medians and IQRs otherwise. Categorical variables will be described as the number and percent of participants in each category (i.e., gender, ethnic group, insulin regimen). Adverse events will be categorised by the type of event (e.g., severe hypoglycaemia, DKA, sensor insertion issues, sensor wear issues). The frequency of events will be reported by event category.

A mixed linear model will be used to test the difference in HbA1c, with the primary outcome being at 6-months, between the intervention and control groups, using data from all time points with a random participant effect used to accommodate the repeated measures and a group-time interaction to model differences in longitudinal changes. Changes in number of glucose measurements performed and patient-reported outcome measures (i.e., PedsQL generic core scale, PedsQL diabetes module, HFS, and DTSQs scores) from baseline through to 6 months will be calculated by comparing scores from control and intervention group participants using Poisson (or negative binomial regression if there is evidence of over-dispersion) for count outcomes and linear mixed models for continuous outcomes with all collected data included. Model residuals will be examined along with the distribution of random effects. If residuals are positively skewed, natural logarithmic transformations will be investigated and retained if these improve the satisfaction of model assumptions. Mixed quantile regression will be investigated for continuous outcomes if issues with model residuals remain following such transformations. If HbA1c values of 130 are observed, mixed Tobit models with right censoring at 130 will be used for this outcome instead. All mixed models will use restricted maximum likelihood (REML) estimation for the variance components.

Some secondary analyses, such as those involving the wait-list control after they cross over, will only include participants from one group and so group (and group-time interaction) terms will not be included in these models.

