The main analyses will follow a modified intention- to-treat principle with all participants analysed in the group to which they were randomised, regardless of actual sensor wear. Per protocol analyses will be also be investigated by including only those from the FGM group who scanned at least 12 out of 14 days in the two weeks prior to the 6-month study visit and excluding any participants from the SMBG group who used FGM at any time during the study. All models will include variables used in minimization [59].

Any missing HbA1c values will be imputed using multiple imputation with chained eqs. (100 imputations after at least 100 burn-ins) and with the imputation model including: gender, HbA1c status at baseline as well as values of that variable from other time points, insulin regimen, frequency of self-monitored glucose (capillary or interstitial) and socioeconomic status. If missing data exceeds 10%, plausible scenarios involving informative missing data will be investigated to explore the robustness of findings.

Statistical analyses will be performed using R 3.5.2 or Stata 15.1 software (or later versions) with two-sided *p* < 0.05 considered significant. To maintain the integrity of the study, statistical analyses will be performed by the biostatistician blinded to group allocation.

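### Statistician blinding is promised through analyses that themselves reveal the arms, and the primary HbA1c analysis may leave the mean-difference scale on residual judgement

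*Protocol article*

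**What the plan says.** **Blinding.** Randomisation: "The statistician will be blinded to allocation arm and will use non-informative group codes until all planned analyses are completed". The end of Statistical analysis repeats that "statistical analyses will be performed by the biostatistician blinded to group allocation".

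**Primary model.** Statistical analysis sets the default: "A mixed linear model will be used to test the difference in HbA1c, with the primary outcome being at 6-months". Three departures follow.
- Log: "If residuals are positively skewed, natural logarithmic transformations will be investigated and retained if these improve the satisfaction of model assumptions".
- Quantile: mixed quantile regression is to be investigated for continuous outcomes if residual problems persist. No quantile is named.
- Tobit: "If HbA1c values of 130 are observed, mixed Tobit models with right censoring at 130 will be used for this outcome instead". The Glycaemic control section explains the ceiling: the analyser reads no higher than 130 mmol/mol.

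It then adds: "All mixed models will use restricted maximum likelihood (REML) estimation for the variance components".

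**Target.** The hypothesis (Aim, objectives and hypotheses) is a reduction of at least 1.0% in mean HbA1c at 6 months. Sample size powers a 1% (10.93 mmol/mol) difference in mean changes.

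**The concern.** There are two separate faults.

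First, the blinding statement covers every planned analysis, and several of those cannot be run without learning which code is FGM. A reader of the trial report would be told of a safeguard that did not operate as described.

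Second, the quantity that the primary analysis estimates is not settled before the data are seen. A log model gives a ratio of geometric means, and quantile regression gives a difference in some unnamed quantile. Neither is the mean difference that the trial hypothesises and is sized for. The move depends on a judgement about residuals, so two competent analysts could report different primary quantities from the same data.

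**Working it through.** **1. Which planned analyses reveal the codes**

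| Planned item | Where | Why it identifies the arm |
|---|---|---|
| Per-protocol set | Aim, objectives and hypotheses; Statistical analysis | FGM participants kept by scanning days, SMBG participants dropped for any FGM use |
| Waitlist-only models after crossover | Statistical analysis | One named arm is analysed |
| Acceptability at 3 and 6 months | Flash glucose monitoring acceptability: "Adolescents in the FGM group will evaluate the FreeStyle Libre FGM system acceptability at 3- and 6-months" | Data exist in one arm only |
| Interstitial scan data | Table 2; Flash glucose monitoring | Before 6 months, generated by FGM users |
| Sensor adverse events | Statistical analysis | The categories apply only to sensor wearers |

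The HbA1c model itself needs only HbA1c, group code, time and the minimisation variables, and none of these names the arm. One input to the primary analysis could leak: the imputation model for missing HbA1c uses monitoring frequency, capillary or interstitial. A label would reveal the arm. An unlabelled count would not do so directly, although a large difference in frequency could hint at it.

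**2. Reproducing the sample size**

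Inputs from Sample size: SD 18.6, correlation 0.7, difference 10.93, two-sided 0.05, power 80%.
- SD of change = 18.6 × √(2 × (1 − 0.7)) = 14.41 mmol/mol.
- Normal approximation: n = 2 × (1.960 + 0.842)² × 14.41² / 10.93² = 27.3, so 28 per group (56).
- t-test: 29 per group (58), with 81.0% power. The stated 58 reproduces.

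**3. What a change of estimand does to power**

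If median regression became primary and errors were normal, its efficiency relative to the mean is 2/π.
- Effective SD = 14.41 × √(π/2) = 18.06.
- At 29 per group, 10.93 / (18.06 × √(2/29)) = 2.30, giving about 62% power by the t-test calculation (63% by normal approximation).
- For 80% power, 27.3 × π/2 = 42.8, so about 43 per group (44 by the t-test).

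On the log scale, 10.93 mmol/mol is not one fixed effect. From an assumed mean of 85 the ratio is 74.07/85 = 0.871; from 95 it is 84.07/95 = 0.885.

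**4. How likely the Tobit rule is to apply**

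The protocol gives no mean HbA1c, so means of 85, 90 and 95 are assumed, with SD 18.6. Let p be the chance that a reading rounds to 130 or more. The chance of at least one among 64 baseline readings is 1 − (1 − p)^64.

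| Assumed mean | Normal: p | Normal: at least one | Gamma shifted to start at 75: at least one |
|---|---|---|---|
| 85 | 0.8% | 42% | 91% |
| 90 | 1.7% | 66% | 95% |
| 95 | 3.2% | 87% | 98% |

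The SD was taken among values of 75 or more, yet a normal curve with these means puts 30% to 14% of readings below 75. The shifted gamma is therefore the more plausible shape. Capping at 130 lowers an arm mean by 0.05 to 0.22 mmol/mol under the normal and by about 0.9 to 1.0 under the gamma.

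**5. Type I error**

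The check was a simplified null simulation: 1,500 runs, 6-month ANCOVA, skewed HbA1c with assumed mean 95, 32 per arm, Monte Carlo SE 0.6 points. Linear gave 5.1%, log 5.1%, median 2.7% and Tobit 5.7%. The written rule gave 5.7% with Tobit and 4.9% without. Taking the smallest of the four p-values gave 6.7%. The median figure is approximate because its solver hit the iteration limit in some runs.

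**The case against.** The strongest reply is that the primary result is safe. The arm-revealing analyses are secondary or tertiary, nothing requires them to be run first, and the HbA1c model can be fitted under codes. This stands. A reader might infer that the primary model will be picked by an unblinded analyst, or that the safeguard is absent. The protocol does not support that: it leaves the order of work unstated, so the safeguard is unsecured rather than missing.

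A reader might also count the Tobit switch as analyst discretion. It is not. Its trigger is any reading of 130, it ignores group, and it answers a documented instrument limit. The Tobit coefficient is also a mean difference in mmol/mol for uncensored HbA1c, so it stays on the powered scale. Section 4 shows that it may well be the model used, which leaves less room for the log and quantile steps.

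Further, the fallbacks are listed in advance, none depends on the treatment effect or its p-value, and exact diagnostic criteria are often left to an analysis plan. This tempers the second fault without removing it. The protocol itself permits the primary quantity to change scale, and its hypothesis and power statement do not follow.

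**Conclusion.** The concern holds in a limited form. Blinding through all planned analyses cannot be achieved by the person who runs them; this follows from the text and needs no assumption. The primary HbA1c estimand is left open to a log or quantile version on residual judgement, while the trial is defined and powered for a mean difference only.

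The consequence for false positives is probably small: 5.7% under the written rule, and 6.7% even when the best of four p-values is taken, in a simplified simulation with an assumed distribution. A claim of serious error inflation would not be supported. The consequence for interpretation and power is larger if quantile regression is adopted: about 81% falls to about 62%, assuming the median and normal errors. That loss would be smaller, or could reverse, under the heavy skew that would prompt the switch.

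The REML sentence is a wording fault only. Mixed Tobit models are ordinarily fitted by maximum likelihood, so the word all is too wide, but no result turns on it.

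**What to change.** 1. **Blinding.** Limit the statement to the primary and other two-arm analyses. Release HbA1c, baseline data and a single unlabelled monitoring count under group codes, sign off the primary result, and only then release scan, acceptability, sensor and post-crossover data.
2. **Estimand.** Fix the primary quantity as the mean difference in HbA1c in mmol/mol at 6 months, from the linear mixed model, or from the already prespecified Tobit model if any value of 130 occurs. Report log and quantile versions as sensitivity analyses, together with the linear model of capped values when Tobit applies. Making the capped linear model primary throughout would be a trade-off rather than a clear gain, since the capping loss could reach about 1 mmol/mol per arm.
3. **Wording.** Limit the REML sentence to linear mixed models.

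The cost is a few sentences, one staged data export, and less freedom to respond to skewed residuals in the primary model. Trial conduct does not change.

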## Methods

### Study design

Managing Diabetes is a ‘Flash’ is a two phase study programme consisting of a multi-centre randomised, parallel-group study consisting of a 6-month comparison between SMBG and FGM, including a 6-month continuation phase (see Fig. 1). Once enrolled, the total study period is 12 months for each participant (12 months of FGM for the intervention group will enable an investigation of sustained FGM outcomes). During the continuation phase, the FGM group will continue the intervention for a further 6 months and the control group will cross over and receive a 6-month FGM intervention. The primary purpose of offering FGM to the control group at 6 months is to encourage retention and engagement.

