• Planned to continue with routine clinical care during the initial 6-month RCT	• Currently using a CGM or FGM device or has used one continuously (other than for intermittent hospital use) within the previous 4 months
• Resident in and expecting to remain in regions affiliated with the Canterbury, Capital and Coast, and Southern District Health Boards for the following year	• Participation in another device or drug study that could affect glucose measurements during the study period
	• Pregnant, lactating, or plan to become pregnant
• Ability to understand study procedures, including English language proficiency, and to comply with them for the entire length of the study	
	• Inability of individual (for those aged 16 years and older) or legal guardian (for those aged 13–15 years) to give written informed consent

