Participants will return in 14 days for the sensor site to be inspected for skin problems, apply the next sensor under supervision, and receive a 3-month FGM supply (i.e., 6 sensors and Rockadex or Hypafix patches). At this 14-day follow-up visit, staff will briefly provide more advanced FGM education on the trend arrows (specifically, the rate of change associated with each arrow direction and arrows indicating the need for a blood glucose check), the target glucose range graph, and instructions to review glucose readings on a computer using a 2-page handout (see Supplementary material). In exceptional circumstances, such as participants living more than 3 h from a clinic, the participant will apply their first sensor under trained staff supervision, receive a 3-month sensor supply, and will be followed-up in 14-days via teleconference software (Zoom, Zoom Video Communications, San Jose, CA, USA). Participants will apply their sensor unsupervised every 2 weeks for the remainder of the study. No further FGM education will be provided and no adjustments to treatment will be made by study staff. Furthermore, study staff will not interfere with participants’ adherence to flash glucose monitoring. Participants will be instructed to seek guidance on scanning frequency from their lead diabetes care provider.

Additional FGM supplies will be provided at the 3-, 6-, and 9-month follow-up visits. During all follow-up visits, retrospective glucose readings will be downloaded from the FGM reader for the previous 2 weeks, and reviewed for glucose levels below 4.0 mmol/mol between the hours of 10 pm and 7 am. All events of nocturnal hypoglycaemia in the previous 2 weeks will be reported to the appropriate diabetes care provider for follow-up.

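### Site is neither a minimisation factor nor a stated model term in this three-district trial, so the arms can differ by chance on who provides local care

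*Protocol article*

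**What the plan says.** The Study design section describes a "multi-centre randomised, parallel-group study consisting of a 6-month comparison between SMBG and FGM". Table 1 limits entry to residents of "regions affiliated with the Canterbury, Capital and Coast, and Southern District Health Boards", so there are three districts.

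Allocation is central, by an offsite biostatistician, "in batches using a 1:1 ratio to either the waitlist control (SMBG) group or the intervention (FGM) group". The factors and the reason for them are stated: "As gender and pre-study HbA1c may significantly affect the primary outcomes, minimisation will be used". The HbA1c factor has two bands, split at 100 mmol/mol. The method runs "with a small random component (20%) along with randomly ordering the participants in each batch used to preserve allocation concealment". Site is not mentioned.

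The Statistical analysis section gives the primary model "with a random participant effect used to accommodate the repeated measures and a group-time interaction to model differences in longitudinal changes". Its covariate rule is: "All models will include variables used in minimization". No site or centre term appears.

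On delivery, the section on the usual care group leaves diabetes care, including SMBG recommendations, with the participant's own clinical team. The FGM group continues the same routine care. On how often to scan, the FGM section says: "Participants will be instructed to seek guidance on scanning frequency from their lead diabetes care provider".

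**The concern.** The Randomisation section selects factors because they may affect the primary outcome, and on the protocol's own description site could meet that test. The comparator is whatever the local team provides. The intervention sits on top of the same local care, and the local provider advises on scanning frequency. The Background links higher scanning rates to better HbA1c.

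Because the model covariates follow from the minimisation list, leaving site off the list also leaves it out of the stated analysis. With 64 participants over three districts, one district can by chance contribute noticeably more to one arm. If HbA1c change differs between districts, part of that difference enters the estimated treatment effect. Even with good balance, between-site variation in change stays in the residual. A visible imbalance beside a borderline result would also invite dispute over an unplanned site adjustment.

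**Working it through.** **Inputs from the protocol (Sample size section).** SD of HbA1c 18.6 mmol/mol; correlation 0.7; target difference 10.93 mmol/mol; two-sided 0.05; 29 per group analysed and 32 per group recruited.

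**Assumptions not in the protocol.** Site sizes and between-site differences in HbA1c change. I take 22/21/21 participants, and mean changes differing by 0/2.5/5 (lower case) or 0/5/10 mmol/mol (upper case).

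**1. The plan's own figure.**
- SD of change = 18.6 × √(2 × (1 − 0.7)) = 14.41.
- Power by the noncentral t distribution is 79.6% at 28 per group and 81.0% at 29, so 29 per group is reproduced.
- Standard error = 14.41 × √(2/29) = 3.78 mmol/mol.

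**2. Chance of a lopsided site.** Take 32:32 allocation unrelated to site, over 22/21/21. A split of 2:1 or worse means at least 14:7 in a site of 21 or at least 15:7 in the site of 22. The probability that at least one site is this uneven is 0.22.

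**3. Size of the resulting shift.** The shift is the sum over sites of (share of the FGM arm − share of the SMBG arm) × site mean change.
- Upper case (0/5/10): SD 1.03 mmol/mol, 90th percentile of the absolute shift 1.7.
- Lower case (0/2.5/5): SD 0.52, 90th percentile 0.86.
- The mean shift over repeated randomisation is zero in both cases.

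**4. Power, if site variance comes on top of the planning SD.**
- Upper case: between-site variance 16.8. Total SD = √(14.41² + 16.8) = 14.98, and power at 29 per group is 78.0%. Site makes up 16.8 / (207.6 + 16.8) = 7.5% of the variance of change.
- Lower case: between-site variance 4.2. Total SD = 14.55, and power is 80.3%.
- If the 18.6 SD already contains site variation, nothing is lost against plan, and adjusting for site would gain a little.

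**5. What balancing on site would do.** Minimisation was simulated 4,000 times per setting with N = 64. The 20% component was read as purely random allocation. Half the participants were male, 35% were in the upper HbA1c band, and sites were equal or 50/25/25 (all assumed).

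| | Site not a factor | Site a factor |
|---|---|---|
| Mean of the largest gap between arms in a site's share | about 14 points | about 4 points |
| Chance of a gap of 15 points or more | 41–43% | under 1% |
| 95th percentile of absolute shift, one site differing by 5 mmol/mol | 1.1–1.3 mmol/mol | 0.4–0.5 mmol/mol |

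The sample size of 58, or 64 recruited, is unaffected.

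**The case against.** The strongest reply is that this is ordinary chance variation in a covariate that was not stratified. It averages to zero, the confidence interval already allows for it, and no stated figure changes. The site effects are assumed, and the upper case spans almost the whole target difference. Differences in HbA1c level between districts hardly matter, because the comparison is of changes within participants. All of this stands and keeps the point small.

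It can also be said that the covariate rule does not forbid a site term and that an unseen analysis plan might add one. That is right, and a reader should not infer that adjustment for site is excluded. The minimisation list is different: the article gives it in full, with its reason, and an analysis plan cannot change how participants were allocated.

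A third reply is that district does not fully capture who gives care, since the physician is paediatric or adult according to age. Balancing on district would leave that split unbalanced. This limits the gain but does not remove it.

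A reader might infer that FGM start-up also varies by clinic. The documents do not support this. The FGM section has staff trained by the distributor, the manufacturer's quick start guide, and common handouts at baseline and at 14 days. The point rests on usual care and scanning advice alone.

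**Conclusion.** The point holds as a minor design weakness. Local providers deliver usual care in both arms and advise on scanning, yet site is absent from minimisation and from the stated models. On near-equal sites, some site splits 2:1 or worse in about 22% of trials. The SD of the resulting shift is about 0.5 to 1.0 mmol/mol under the assumed site differences, against a standard error of 3.8 and a target of 10.93. Power falls to about 78% at worst, from 81%, and only if site variance is not already in the planning SD.

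It would be tempting to say that clinic differences would be mistaken for a device effect. The documents support only a chance shift in either direction, not a biased trial. Site sizes and site effects are assumptions throughout.

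**What to change.** In the Randomisation section, add district health board (three levels) as a third minimisation factor. Under the existing covariate rule it then enters every model as a fixed effect. If baseline HbA1c is one of the repeated responses, as the use of all time points suggests, a site main effect adjusts level but not change. The site term should then also interact with time.

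If allocation is under way or complete, leave the allocation rule unchanged, prespecify site as a fixed-effect covariate before unblinding, and report arm by site.

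The cost is one more field in a central routine that already exists, two degrees of freedom for site (two more for each follow-up time if it interacts with time), and marginally looser balance on gender and HbA1c band. The recruitment target stays at 64.
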